# The effect of opioid-free anesthesia protocol on the early quality of recovery after major surgery (SOFA trial): study protocol for a prospective, monocentric, randomized, single-blinded trial

**DOI:** 10.1186/s13063-021-05829-x

**Published:** 2021-11-27

**Keywords:** Anesthesia, Opioid-free anesthesia, Opioid-related adverse effects, Quality of recovery, Quality of life, Perioperative care, Patient-reported outcome measures

## Abstract

**Background:**

Since the 2000s, opioid-free anesthesia (OFA) protocols have been spreading worldwide in anesthesia daily practice. These protocols avoid using opioid drugs during anesthesia to prevent short- and long-term opioid side effects while ensuring adequate analgesic control and optimizing postoperative recovery. Proofs of the effect of OFA protocol on optimizing postoperative recovery are still scarce. The study aims to compare the effects of an OFA protocol versus standard anesthesia protocol on the early quality of postoperative recovery (QoR) from major surgeries.

**Methods:**

The SOFA trial is a prospective, randomized, parallel, single-blind, monocentric study. Patients (*n* = 140) scheduled for major plastic, visceral, urologic, gynecologic, or ear, nose, and throat (ENT) surgeries will be allocated to one of the two groups. The study group (OFA group) will receive a combination of clonidine, magnesium sulfate, ketamine, and lidocaine. The control group will receive a standard anesthesia protocol based on opioid use. Both groups will receive others standard practices for general anesthesia and perioperative care. The primary outcome measure is the QoR-15 value assessed at 24 h after surgery. Postoperative data such as pain intensity, the incidence of postoperative complication, and opioid consumption will be recorded. We will also collect adverse events that may be related to the anesthetic protocol. Three months after surgery, the incidence of chronic pain and the quality of life will be evaluated by phone interview.

**Discussion:**

This will be the first study powered to evaluate the effect of OFA versus a standard anesthesia protocol using opioids on global postoperative recovery after a wide range of major surgeries. The SOFA trial will also provide findings concerning the OFA impact on chronic pain incidence and long-term patient quality of life.

**Trial registration:**

ClinicalTrials.gov NCT04797312. Registered on 15 March 2021

## Background

Opioids play an essential part in pain control during anesthesia, even in the “balanced anesthesia” concept. However, opioids are associated with many side effects (e.g., nausea, vomiting, ileus, sedation, delirium, addiction, hyperalgesia) [1]. Since the 2000s, opioid-free anesthesia (OFA) protocols have been spreading worldwide in anesthesia daily practice. These protocols avoid using opioid drugs during anesthesia to prevent short- and long-term opioid side effects while ensuring adequate analgesic control and optimizing postoperative recovery.

The emergence of OFA protocols parallels the emergence of an “opioid crisis” (i.e., a dramatic increase in opioid addiction and of related death), particularly in the USA, with a significant proportion of treatment initiation during the perioperative period [2, 3]. This lead scientific societies to reduce patients’ exposure to opioids [4]. OFA is based on a multimodal combination of nonopioid agents such as N-methyl-d-aspartate antagonists, anti-inflammatory drugs, local anesthetics, and alpha-2 agonists. Currently, the anesthetic literature regarding OFA remains controversial, with studies confirming or not its benefit [5–8]. The most recent randomized controlled study published is negative but focused only on opioid-related adverse events [9].

Suggested effects reported in previous studies of multimodal use of OFA are intraoperative hemodynamic stability [10], analgesic efficacy [11, 12], and decreased opioid-associated adverse effects (especially on postoperative nausea and vomiting) [13–15]. The application of OFA protocols could also address other effects of opioid use, such as addiction, development of pain chronicity, or even immunomodulation that may negatively impact postoperative infection or cancer [16]. Combining all these benefits may improve the overall quality of postoperative recovery (QoR) [11]. In addition, no data are available on longer-term outcomes.

We aim to perform a study to determine the impact of an OFA protocol versus standard of care (i.e., opioid use during anesthesia) on the QoR after major surgeries.

## Methods

In this superiority, randomized, controlled, single-blinded, single-center trial, we plan to include patients scheduled to undergo elective major surgery (plastic, visceral, urologic, gynecologic, or ENT surgeries). The patients will be allocated to receive either an OFA protocol or a standard anesthesia protocol (Fig. 1). The study will be conducted at the Angers University Hospital, Angers, France. This trial is designed following the Standard Protocol Items (SPIRIT guidelines). Figures 2 and 3 provide an overview of the study plan.

**Fig. 1 Fig1:**
[figure not shown]
Detailed interventional protocols in the opioid-free anesthesia group (OFA group) and in the standard anesthesia group (English translation from our French procedures). IV, intravenous; PACU, postanesthesia care unit

**Fig. 2 Fig2:**
[figure not shown]
Standard Protocol Items: Recommendations for Interventional Trials (adapted from SPIRIT figure). BPI, Brief Pain Inventory; D7, 7 days after surgery; D30, 30 days after surgery; H24, 24 hours after surgery; H48, 48 hours after surgery; H72, 72 hours after surgery; M3, 3 months after surgery; OFA, opioid-free anesthesia; PACU, postanesthesia care unit

**Fig. 3 Fig3:**
[figure not shown]
Flow chart

The French Institutional Review Board “Eastern III” (Nancy, France, number: 2021-A00364-37) and the National Agency for Drug and Health Product Safety have approved the study protocol (2021-A00364-37) in its version 1. Patients will provide written consent for participation. The study will be conducted in accordance with the Declaration of Helsinki.

### Participants

Eligible patients are adults (age ≥ 18 years) undergoing a scheduled surgery with an estimated time of 90 min or more and supposed to be painful (with the usual need for postoperative intravenous (IV) morphine patient-controlled analgesia (PCA)). The surgical specialties concerned are ENT, plastic, digestive, urologic, and gynecologic surgery. Eligible patients must be French-speaking and must have sufficient cognitive ability to complete a questionnaire. The exclusion criteria are surgery with an orthopedic procedure (e.g., osteosynthesis), need for rapid sequence anesthetic induction, pregnancy or lactation, severe psychiatric or cognitive disorder interfering with questionnaire assessment, body mass index < 18 or > 39 kg/m^2^, any contraindication to study drugs, porphyria, uncontrolled epilepsy, unstable cardiac insufficiency, chronic renal or hepatic failure, preoperative bradycardia with an atrioventricular block (2nd or 3rd degree), chronic beta-blocker treatment, and ongoing treatment with a QT interval prolonging drug.

### Information of patients

During the anesthesia consultation, investigators will verify inclusion/exclusion criteria. The investigator will invite the patients to participate. Patients will receive complete information in faithful terms and understandable language concerning the objectives, the required follow-up, the risks, the safety measures, and the right to refuse to participate or stop the study at any time. The investigator obtained written informed consent signed by both the investigator and the patient.

### Randomization and blinding

The included patients will be randomized to one of the two groups (OFA or standard of care) using a web-based system (Ennov Clinical® software) by the investigator anesthesiologist in charge on the day or the day before the scheduled surgery.

Patients will be randomized in one of the two groups with a 1:1 ratio, using a minimization algorithm defined by the randomization methodologist (with a probabilistic component), based on two factors: the type of surgery (ENT, plastic, digestive, urologic and gynecologic surgery) and the surgery severity (assessed by the Surgical Outcome Risk Tool (SORT) score, which can be classified in minor, intermediate, major and major/complex surgery, and which is available online at www.sortsurgery.com). Investigators do not know this equation and will not be able to guess the next randomization arm.

The anesthesia team performing the general anesthesia will be unblinded on the allocation group. The patient will be kept blinded to the protocol allocation, as the nurses and the medical team involved in the postoperative care and outcomes evaluation. For outcomes requiring a phone call, evaluators will be blinded to the allocation group.

### Intervention

The study aims to compare an OFA protocol to an anesthesia protocol based on standard practices. In both arms, patients will undergo general anesthesia, combined or not with local or regional anesthesia. The two protocols are detailed in Fig. 1.

None of the patients will receive premedication. Anesthetic monitoring will be the same in both groups, including pulse oximetry, electrocardiography, non-invasive blood pressure and/or invasive monitoring when indicated, body temperature, muscle relaxation (train-of-four stimulation), and bispectral index.

The OFA protocol (OFA group) begins before surgery with a clonidine infusion (under cardiac monitoring) at an initial rate of 50 μg/h, and then adapted according to hemodynamic stability (to keep systolic blood pressure in a range of ± 20% its basal value) with a maximal rate of 150 μg/h (100 μg/h for patients with body weight < 50 kg). Anesthesia will be induced and maintained with hypnotic drugs and curare left at the anesthesiologist’s discretion. No opioids should be infused. The clonidine infusion should be continued at the same infusion rate. The OFA protocol includes a magnesium sulfate infusion (40 mg/kg), a lidocaine infusion (1.5 mg/kg bolus dose in 10 min followed by 1.5 mg/kg/h continuous infusion), and a ketamine infusion (0.5 mg/kg bolus dose followed by a 0.2 mg/kg/h continuous infusion). The ketamine infusion should be stopped 30 min before the end of the surgery, and the lidocaine infusion will be stopped after 1 h in the postanesthesia care unit (PACU).

The standard anesthesia protocol associates hypnotic drugs, curare, and opioids (sufentanil or remifentanil) left at the discretion of the anesthetist in charge. A low-dose ketamine bolus (0.15 mg/kg) is allowed at anesthesia induction, possibly followed by repeated boluses since it is commonly used in our standard practice.

In both arms, according to recent recommendations, anesthesiologists are prompted to infuse an antimicrobial prophylaxis [17], to apply a protective ventilation strategy (tidal volume between 6 and 8 ml/kg, respiratory rate for an end-tidal CO_2_ value at 35–40 mmHg, a positive end expiratory pressure) [18], and to treat perioperative hypotension and hypovolemia [19]. The depth of anesthesia is monitored by a bispectral index sensor (target 40–60). Postoperative pain, nausea, and vomiting are managed according to the unit protocols. The use of local or regional anesthesia is allowed in both groups (in the OFA group, the protocol stipulates not to use opioids as adjuvant). In the PACU, if the patient experiences acute pain (defined as a pain analog scale ≥ 4), morphine or oxycodone titration will be started (bolus of 1 to 2 mg, with a 5-min delay between two doses) until pain relief is achieved. The analgesic management will be continued in the ward using IV PCA and/or oral opioids. The doses of opioids (i.e., morphine and oxycodone) will be converted into morphine-equivalent doses according to the following rule: 1 mg oral morphine = 1/2 mg oral oxycodone = 1/3 mg IV morphine; 1 mg IV morphine = 1 mg IV oxycodone. Patients will be discharged to the ward when their modified Aldrete score is ≥ 12 [20].

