#### Secondary outcomes

In order to confirm the impact of the OFA protocol on postoperative recovery, we will also measure the QoR-15 score at 48 h and 72 h after the surgery in all patients. We will evaluate the pain during effort (mobilization, cough or physiotherapy sessions) and the number of postoperative complications according to the POMS (postoperative morbidity survey) classification [27], assessed up to 72 h after the surgery. The postoperative consumption of morphine-equivalent will also be compared between the two groups. The lengths of stay in PACU and in the hospital will be measured.

We will compare the patient tolerance to the allocated protocol with the assessment of the hemodynamic status (intra-operative use of vasopressor or cessation of one of the drugs for hemodynamic purposes), heart-rhythm (< 35 or > 140 beats per minute for more than 30 s), and anaphylactic reactions. Another secondary outcome is the respect of the allocated protocol by the anesthesia team: OFA protocol will be considered complete if at least two of the following drugs are used between ketamine, lidocaine, clonidine, and magnesium sulfate, and if no intraoperative opioids are used; the standard group will be considered complete if lidocaine, clonidine, or magnesium sulfate are not used intra-operatively. The surgeon’s and anesthesiologist’s satisfactions concerning the anesthesia will be assessed after the surgery according to a numerical scale (rated from 0 to 10). We will also compare the patient satisfaction of anesthesia at 24 h via a numerated scale from 0 to 10 (0 = not satisfied and 10 = totally satisfied) and the presence or absence of intra-operative memorization.

Three months after surgery, a phone interview will be conducted to evaluate the chronic pain using the Brief Pain Inventory (BPI) [28] in its French short version, the quality of life using the French EQ-5D-3 L questionnaire (available on request on https://euroqol.org/), and the rate of neuropathic pain diagnosed using the DN-4 questionnaire [29].

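### A lidocaine infusion that runs for 1 h in the PACU in the OFA arm only, with no masking described, conflicts with the claim that postoperative staff are blinded and may set an arm-specific minimum on PACU stay

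*Protocol article*

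**What the plan says.** The Intervention section gives the OFA arm "a lidocaine infusion (1.5 mg/kg bolus dose in 10 min followed by 1.5 mg/kg/h continuous infusion"), and then states that "the lidocaine infusion will be stopped after 1 h in the postanesthesia care unit (PACU").

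The comparator is described differently: "The standard anesthesia protocol associates hypnotic drugs, curare, and opioids (sufentanil or remifentanil) left at the discretion of the anesthetist in charge". It contains no lidocaine, and no dummy infusion is mentioned. The adherence rule under Secondary outcomes adds that "the standard group will be considered complete if lidocaine, clonidine, or magnesium sulfate are not used intra-operatively". For the OFA arm the same rule is looser: "OFA protocol will be considered complete if at least two of the following drugs are used between ketamine, lidocaine, clonidine, and magnesium sulfate", provided no intraoperative opioid is given.

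Under Randomization and blinding, only the team giving the anesthetic is named as unblinded. The patient is blinded, "as the nurses and the medical team involved in the postoperative care and outcomes evaluation". Telephone assessors are blinded too.

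On PACU stay, Secondary outcomes says "The lengths of stay in PACU and in the hospital will be measured", and Statistical analysis compares it between arms by linear regression on allocation and the minimization factors. The Intervention section gives one discharge criterion for both arms: "Patients will be discharged to the ward when their modified Aldrete score is ≥ 12". That sentence does not mention the infusion. According to Follow-up, the PACU record also holds analgesic dose, complications including nausea and vomiting, and a numerical pain score.

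**The concern.** Two statements meet in the PACU and do not fit together. One says that postoperative nurses and doctors do not know the allocation. The other has them looking after an infusion that belongs to one arm. These staff titrate the rescue opioid, record complications and decide when the patient leaves. If they can infer the arm, those results would be published under a blinding claim that the intervention text does not support.

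The second issue is what PACU length of stay measures. If an OFA patient who already meets the discharge criterion is kept until the infusion ends, part of the between-arm difference comes from the infusion schedule and not from speed of recovery. The effect would lengthen stay in the OFA arm.

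**Working it through.** **Blinding: the statements side by side**

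1. Lidocaine is running on arrival in the PACU and for 1 h afterwards in the OFA arm (Intervention).
2. Intra-operative lidocaine in the standard arm makes that patient non-adherent (Secondary outcomes). A lidocaine infusion carried into the PACU therefore points almost uniquely to OFA.
3. The reverse inference is weaker. An OFA patient can be adherent on two of the four drugs, so the absence of lidocaine does not prove standard allocation.
4. No masking is described, and the blinding statement has no PACU exception.

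As the article stands, points 1, 2 and 4 cannot be squared with blinded PACU staff.

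**PACU stay: size of a possible minimum**

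The plan gives no figure for PACU stay, so there is none to reproduce and the size rests on assumptions.

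Assumptions: without the infusion, stay X is lognormal with median m and log-SD s in both arms (no true difference). Every OFA patient receives lidocaine and stays at least c = 60 min. The OFA stay is then max(X, 60), and the mean rises by

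E[(60 − X)⁺] = 60·Φ(d) − m·exp(s²/2)·Φ(d − s), with d = ln(60/m)/s.

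The share of patients who would otherwise leave before 60 min is Φ(d).

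Worked case, m = 60 and s = 0.4: d = 0, Φ(0) = 0.5, m·exp(0.08) = 65.00, Φ(−0.4) = 0.3446. Shift = 60 × 0.5 − 65.00 × 0.3446 = 30 − 22.40 = 7.60 min.

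| Assumed median (min) | Share under 60 min, s = 0.4 to 0.6 | Added to OFA mean (min), s = 0.4 to 0.6 |
|---|---|---|
| 60 | 50% | 7.60 to 10.30 |
| 75 | 29% to 36% | 3.57 to 6.43 |
| 90 | 15% to 25% | 1.65 to 4.09 |
| 120 | 4% to 12% | 0.35 to 1.75 |

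If only a fraction π of OFA patients receive lidocaine, and receipt is unrelated to stay, each shift is multiplied by π. The table is therefore an upper bound for its assumptions.

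**Effect on the test**

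This was simulated with 70 patients per arm, no true difference, s from 0.3 to 0.7, and a two-sample t-test standing in for the planned regression, with 10,000 trials per setting. The rejection rate at a nominal 5% was:

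- median 45 min: 72% to 100%
- median 60 min: 25% to 56%
- median 90 min: 5.5% to 6.3%
- median 120 min: 4.6% to 5.4%
- median 180 min: 4.8% to 5.1%

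The minimum matters only if a substantial share of patients would otherwise leave within about an hour.

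**The case against.** The strongest reply has four parts.

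*The minimum is inferred.* A reader might infer that OFA patients must stay 1 h whatever their Aldrete score. The documents do not say so. One sentence gives the stop time of the infusion, another gives the discharge criterion, and neither refers to the other. OFA patients without lidocaine are not touched at all. This stands, so the conclusion on stay is conditional.

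*The size may be trivial.* Entry requires surgery of at least 90 min that usually needs morphine PCA, which gives no reason to assume short stays. With medians of 90 to 120 min the shift is at most about 4 min and the test keeps nearly its nominal level. Stay is recorded in hours, so such shifts may be hard to see. This stands, but the documents do not fix the median, so the larger figures cannot be ruled out either.

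*Masking may exist.* A reader might infer that PACU staff cannot be blinded and that pain outcomes are open-label. The article condenses a longer protocol, and Fig. 1, which is not available here, may describe masking. The pain score is ordinarily the patient's own, and the patient is blinded. Titration starts at a fixed threshold, and the listed pain outcome is effort pain followed to 72 h, mostly on the ward. These points limit the exposure. They do not reconcile the blinding statement with the intervention text.

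*Actual stay is a legitimate outcome.* The trial compares whole strategies. If the infusion prolongs PACU stay, that is a real consequence of the strategy and relevant to resource use. This stands, and it is why actual stay should be kept. Likewise, ward opioid dose should not replace total dose, because it depends on earlier PACU titration.

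**Conclusion.** The blinding part holds on the text and needs no assumed figure: as written, the claim that postoperative staff are blinded does not hold for PACU staff caring for a patient on lidocaine, unless the full procedures mask the infusion. What is exposed is PACU opioid titration, PACU complications and the discharge decision.

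The PACU-stay part holds conditionally. If OFA patients stay to complete the infusion, the comparison partly measures the schedule. Under lognormal stays with log-SD 0.4 to 0.6 and lidocaine given to all OFA patients, the OFA mean rises by about 8 to 10 min at a median of 60 min and by about 0.4 to 4 min at 90 to 120 min. Which applies cannot be told from the documents.

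A reader might go further and infer that the trial's main conclusion is compromised. The documents do not support that. The primary outcome is reported by a blinded patient at 24 h, and PACU stay is not among the endpoints that the text places in the hierarchical scheme (QoR-15, chronic pain by BPI, EQ-5D visual analog score). The point deserves correction but does not threaten the primary analysis.

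**What to change.** 1. **Blinding statement.** List PACU staff as not blinded, with ward staff and telephone assessors blinded; or state how the infusion is masked.
2. **Reconcile** the infusion stop time with the PACU discharge criterion, so that the reader knows whether one can delay the other. No change to either is proposed here.
3. **PACU stay.** Add time from PACU arrival to the first modified Aldrete score of 12 or more as the recovery comparison, with the same regression. Keep actual stay beside it and read it as a consequence of the whole strategy.
4. **Opioid dose.** Report PACU and ward doses separately in addition to the total, and label the PACU part as not blinded unless masking is documented.

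The cost is one time field in the eCRF for a score that is already assessed, some protocol wording, and a less favourable blinding claim. Sample size, treatment and the primary analysis are unchanged.

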### Outcomes

#### Primary outcome

The primary outcome is the early postoperative quality of recovery, assessed via the French version of the QoR-15 questionnaire score (FQoR-15) [21], and measured at 24 h after the surgery (postoperative day 1, POD 1). The QoR-15 score is currently the most reliable and reproducible tool to determine the quality of postoperative recovery [22–24]. Its use is recommended to assess the patient’s well-being, according to a recent international consensus [25] and has already been assessed by previous studies [26].

The FQoR-15 score is obtained via a self-administered questionnaire (which can also be performed through a phone interview) and consists in 15 items scored on an 11-point scale, with a total score (sum of each item) range from 0 to 150 (0 for very bad recovery and 150 for an excellent quality of recovery). The FQoR-15 questionnaire is given by the nurses in the ward on a paper sheet and is filled by the patient.

